#### Treatment as usual (TAU) control group

Patients who will be randomized to the "treatment as usual" group will receive routine care. In most cases this consists of an assessment by a casualty doctor or a junior psychiatrist in the emergency department, on the basis of which about one third patients are referred for follow up to psychiatry outpatient, a small number are referred to addiction services, and the remainder are advised to consult their own general practitioner. Patients are not routinely referred to psychotherapy or psychology services [23]. British South Asian self harm patients are more likely to be referred back to their GP as compared to white self harm patients [24]. Participants will receive an initial assessment along with treatment as usual (TAU) as ascertained by the general practitioner or mental health professional. Any type of treatment apart from C-MAPS will be permitted. We will record the details of treatment as usual received and degree of adherence by the patient. Basic demographic information will be recorded for both groups.

### Sample Size

The participants will be randomized to two groups: intervention or treatment-as-usual. A total of thirty participants will be recruited to the pilot. This will ensure that, even after loss to follow-up, we will have at least 10 subjects per group for analysis (FDA guidance http://www.fda.gov/cder/guidance).

### Outcome measures

#### Primary outcome measure

*Beck scale for suicidal ideation: *A 21-item self-report questionnaire used to detect and measure severity of suicide ideation [25]

#### Secondary outcome measures

*Beck hopelessness scale: *Consists of 20 self report questions designed to measure three major aspects of hopelessness; feelings about the future, loss of motivation and expectations [26].

*Beck Depression Inventory: A *21 item self-reported scale to measure the severity of depression [27]

*Euroqol (EQ-5D) Quality *of life - Standardised instrument for use as a measure of health outcome [28] It is a measure of health and quality of life. This is a standardised instrument for use as a measure of health outcome; it provides a simple descriptive profile and a single index value for health status. EQ-5D consists of a self-report questionnaire of five health dimensions (mobility, self-care, usual activities, pain/discomfort and anxiety/depression). We have previously used this instrument with South Asians living in the UK [29]

*Client service receipt inventory (CSRI*) - an estimate of the health and social services received for power calculation (formal and informal such as faith healers). It will also include personal costs e.g. non-attendance at work [30].

*Time to self reported repetition of self harm *(estimate for definitive trial) [31]

*Problem solving Inventory *- Assess individual's perceptions about how they react to and solve personal problems [32]

*Coping resource Inventory *- Assess coping resources available to individual to manage stress [33]

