**Discussion:**

This study will test the feasibility and acceptability of the C- MAP in British South Asian women. We will be informed on whether a culturally adapted brief psychological intervention compared with treatment as usual for self-harm results in decreased hopelessness and suicidal ideation. This will also enable us to collect necessary information on recruitment, effect size, the optimal delivery method and acceptability of the intervention in preparation for a definitive RCT using repetition of self harm and cost effectiveness as primary outcome measures.

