### Aims and objectives

In preparation for a future definitive randomized control trial using repetition of self harm and cost effectiveness as the outcome measures, in this pilot trial we aim to collect necessary information on the assessment instruments, effect size, the optimal delivery and acceptability of the intervention. We also want to gauge the optimum length of treatment and to evaluate the therapy in a preliminary way to see if we can determine a treatment effect.

A further aim is to determine whether C- MAPS compared with treatment as usual results in decreased hopelessness and suicidal ideation. We will explore the impact of the intervention on patient's resolution of interpersonal and family problems to fully understand the mechanism of action of C- MAPS.

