##### Quantitative Analysis

An intention to treat analysis will be carried out. Both parametric and non-parametric tests will be used for data analysis. Mean and standard deviation scores for all continuous measures shall be presented, and normality will be assessed using Kolmogrov-smirnov test for normality. Spearman's correlation coefficient shall be used to measure associations among different measures. Baseline differences will be measured using a t test for normative data and Chi square test for categorical data. This will enable us to take into account any baseline differences in our final analyses. Differences between the treatment and the control group will be measured using linear regression, while controlling for baseline differences.

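### Linear regression is stated for all treatment differences without exception, but time to repetition of self-harm will be right-censored and needs its own analysis

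*Protocol article*

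**What the plan says.** Secondary outcome measures (Protocol article) includes "Time to self reported repetition of self harm", with the note "estimate for definitive trial". Aims and objectives describes the pilot as "In preparation for a future definitive randomized control trial using repetition of self harm and cost effectiveness as the outcome measures", and the Discussion paragraph of the Abstract likewise refers to a "definitive RCT using repetition of self harm and cost effectiveness as primary outcome measures". The pilot's primary outcome is a different one, the Beck scale for suicidal ideation.

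On analysis, the Quantitative Analysis section commits to intention to treat and then states: "Differences between the treatment and the control group will be measured using linear regression, while controlling for baseline differences". For description it says: "Mean and standard deviation scores for all continuous measures shall be presented". It also says, in general terms: "Both parametric and non-parametric tests will be used for data analysis". No test in that last sentence is tied to an outcome. The article does not mention censoring, Kaplan-Meier, log-rank or Cox methods.

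The Methods paragraph of the Abstract places outcome assessments at 3 and 6 months. The Sample Size section recruits 30 women so that at least 10 per group remain after loss to follow-up.

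**The concern.** Time to repetition is observed only for women who report a repeat episode while under follow-up. For everyone else it is known only to exceed the time to last contact. Ordinary linear regression needs one completed value per woman and cannot represent that partial information. An analyst who follows the sentence on treatment differences as written must choose between two codings, neither of which the article acknowledges:

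- Analyse only women with an event. The comparison is then restricted by something that happens after randomisation and that treatment is meant to affect, contrary to the stated intention-to-treat principle.
- Enter follow-up time as the outcome for women without an event. A woman lost early is then treated as if she had repeated early.

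At stake is the planning information on repetition, which the definitive trial is to use as a primary outcome. The pilot's own primary outcome is a scale score, and this point does not affect it.

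**Working it through.** **Inputs from the Protocol article.** Last assessment at 6 months; 30 women in total; at least 10 per group expected after loss. There is no repetition rate, hazard ratio or loss rate, and no stated figure to reproduce for this outcome.

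**Assumptions.** Constant hazard; hazard ratio 0.5; control 6-month risk p varied from 10% to 70%. These are illustrative.

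**Formulas.** λ = −ln(1 − p)/6 per month in the control arm and λ/2 in the intervention arm; S = exp(−6 × hazard).
- Mean time among repeaters: 1/hazard − 6S/(1 − S).
- Mean with event-free women set to 6 months: (1 − S)/hazard.

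**At p = 30%.** λ = 0.3567/6 = 0.0594.
- Control repeaters: 16.82 − 6(0.700)/0.300 = 16.82 − 14.00 = 2.82 months.
- Intervention: S = 0.8367, risk 16.3%; repeaters: 33.64 − 6(0.8367)/0.1633 = 2.91 months.
- Difference among repeaters: 0.09 months.
- With event-free women set to 6 months: 5.50 − 5.05 = 0.45 months.

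**Over the range:**

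| Control risk | Intervention risk | Repeaters only: control mean (months) | Repeaters only: difference | Event-free set to 6: difference |
|---|---|---|---|---|
| 10% | 5.1% | 2.95 | 0.03 | 0.15 |
| 20% | 10.6% | 2.89 | 0.06 | 0.30 |
| 30% | 16.3% | 2.82 | 0.09 | 0.45 |
| 50% | 29.3% | 2.66 | 0.17 | 0.74 |
| 70% | 45.2% | 2.41 | 0.29 | 1.02 |

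A simulation with 1,000,000 women per arm gave 0.02 to 0.30 months for the repeaters-only difference, which agrees within simulation error. While the control risk rises sevenfold, the repeaters-only control mean moves only from 2.95 to 2.41 months. It therefore says little about how often women repeat.

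**Effect of early loss on the second coding.** Assume equal allocation, 15 per arm. One woman last seen at 3 months, who would otherwise have been event-free to 6 months, is entered as 3 instead of 6. That lowers her arm's mean by (6 − 3)/15 = 0.20 months, against a contrast of 0.45 months at 30% risk.

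**How many women lack an event.** Expected events among 30 at assumed risks of 10%, 20%, 30%, 40% and 50% are 3, 6, 9, 12 and 15. The probability that 16 or more of the 30 are event-free is above 0.999 at 10% and 20%, 0.98 at 30%, 0.82 at 40%, 0.43 at 50% and 0.10 at 60%.

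**The case against.** The strongest reply is that the article never assigns linear regression to this outcome by name. The analysis paragraph is condensed, its mention of scores suits the questionnaires, and its reference to parametric and non-parametric tests could be elaborated elsewhere. An article may leave a survival method and a censoring rule to a full protocol or analysis plan. This stands in part: the absence of a named survival method is not itself the fault, and nothing here shows that a fuller document lacks one. What remains is that the article states a method for treatment differences with no exception, and that method does not suit an outcome it lists. The general sentence on tests ties no survival method to repetition.

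Some stronger readings are tempting, and the documents do not support them:

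- *Most women will have no event.* No repetition rate is given. This is likely at assumed risks up to about 40%, but not at 50% or above.
- *Either coding is simply invalid.* With complete 6-month follow-up, setting event-free women to 6 months estimates a difference in restricted mean time, which is interpretable. It fails when women are lost before 6 months without an event.
- *The pilot cannot yield an event rate.* Recording time to repetition means recording whether it occurred, so the number and proportion repeating can still be counted. The article just does not commit to reporting them.
- *This is the only outcome meant for planning.* The service receipt inventory is also listed as an input to a power calculation.

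Finally, wide uncertainty is not evidence against the regression. If 6 of 30 women repeated, the exact 95% interval would be 7.7% to 38.6%. That reflects the sample size and would be wide under any method.

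**Conclusion.** The point holds as a method stated too broadly. Applied literally to time to repetition, linear regression either discards event-free women or treats follow-up time as event time. Under the first coding, a halved hazard appears as about 0.09 months at an assumed 30% control risk, and as no more than about 0.3 months for risks up to 70%. Under the second, the result is a restricted mean difference if follow-up is complete, and is distorted by early loss otherwise. The figures rest on an assumed constant hazard, hazard ratio and risks. The conclusion itself needs only some censoring, which a 6-month limit with expected loss makes all but certain.

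Severity is moderate to minor. One secondary planning outcome is affected, the primary scale outcome is not, and any estimate of repetition from 30 women will be imprecise.

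**What to change.** Amend the Quantitative Analysis section so that linear regression and mean/SD apply to the scale scores only. For repetition of self-harm, state that:

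- the number and proportion repeating by 6 months will be reported by arm with confidence intervals, as the planning quantity;
- Kaplan-Meier curves by arm will run from randomisation, with women who have not repeated censored at last contact;
- any hazard ratio will be given with its confidence interval as descriptive only.

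The cost is a few sentences of analysis wording, plus recording the date of each reported episode and the date of last contact at the 3- and 6-month assessments already planned. The dates should be collected prospectively, because they may not be recoverable later. The sample size does not change.

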### Translation and Cultural adaptation of outcome measures

Translation: All these scales have also been translated into target languages based on our previous work.

### Qualitative Study

The qualitative component of this study will enable a richer picture to emerge and will contribute to an overall understanding of the key issues relating to self-harm in British South Asian women across the study sites. It will document a range of perspectives with treatment providers and users [34]

### Aims and purpose

The aim of the qualitative study is to explore the experience of the patients and therapists to further refine the therapy manual.

We will carry out qualitative in depth interviews with those who complete the intervention and those who drop out of therapy. This is a central part of the qualitative study as we consider the experiences of British South Asian women in contact with services as crucial to more effective and sensitive services [35]

Additionally focus groups will be conducted with the therapists to triangulate data. The aim of these interviews and focus group (s) will be

1. To see what works in therapy and what does not work

2. Which part of therapy the patients find useful

3. Which parts/techniques they don't find too helpful or too alien and which should be addressed in future work for further adaptation

4. Their overall experience of the service and treatment

### Study Participants

1. **Group 1: **Patients who have completed therapy will be interviewed to explore their experience of therapy. This will help us to understand patient's perception of therapy, the techniques they found useful and techniques that were not very helpful. We will also ask them whether there was anything outside therapy they found useful to see if it can be incorporated into therapy. These interviews will further explore the characteristics in therapist they found were helpful or unhelpful. Interviews will be conducted until data saturates, however, we will stop interviews after 7-8 patients have been interviewed due to resource issues. Based on our previous experience however we feel that this number will give us sufficient information to further refine our manual. These interviews will also explore the pathways to care and treatment experience of this group in order to see whether that can be taken into consideration to further improve engagement in therapy and treatment in general.

2. **Group 2: **Patients who drop out of therapy will be asked for their permission to be interviewed. Those who agree will be interviewed to explore the reasons for dropping out of therapy and whether they found anything useful and what could be done to improve engagement with therapy. We expect a number similar to the first group will be required in this group.

3. **Group 3: **This group will consist of mental health professionals who have provided therapy to patients. The idea is to explore their experience of providing therapy, what did they think work and what need to be changed for further improving assessment, engagement and making a positive change in patients lives in future. We will conduct a focus group with these therapists. Therapists will be encouraged to write regular diaries as field notes of any difficulties and this information will be used to further enhance our understanding. These focus groups will further explore their experiences of delivering the intervention; perceptions of gaps in the manual/delivery, what skills they think are needed for effective delivery, perceptions of the impact of race/gender/age of therapist on the intervention. This set of interviews will also help to identify the kinds of difficulties encountered by health care staff in working with this group of patients, and make recommendations to improve services.

### Procedure

Interviews will be semi structured and will be held in English where possible and in a culturally sensitive manner. In cases where interviews are conducted in Urdu, Hindi, Punjabi transcripts will be translated in English language. Interviews are considered as more appropriate for patients due to the high stigma attached to mental illness in this group, and based on our previous work, which suggests that participants of group might hesitate in sharing their experiences. Therapists will be asked to share their opinion through focus group. This is because this is a homogenous group and will be more cost effective. Additional information gathered through the field's notes and supervision notes will also be included in final analyses to guide our final refinements of the manual. Interviews and focus groups will be conducted using interview guidelines; however, we will keep an open mind and explore any newer ideas, which arise during the interviews or focus groups if they are considered to be relevant. This will help us in keeping our focus on the main aim of this part of the study, i.e., refinement of the therapy manual.

These three qualitative elements of the study will enable a much broader picture of the issues to emerge and will complement the quantitative component.

#### Data Analysis

Each interviewer will start analyzing the interviews as and when they are conducted. Analysis involves the researcher immersing him in data by reading the interview transcripts carefully several times, and identifying emerging themes and categories [36]. Where required, interviewers will contact the participants by phone or in person to clarify points and emergent themes that arise from the initial transcriptions or analysis. Interviewers will meet regularly for supervision and support throughout the study. During these meetings emerging themes, concepts and conflicts will be discussed. Interview transcripts will help us in guiding further interviews to clarify themes. This process will be repeated, thus modifying the working codebook till a final set of codes will be obtained. The process will stop when saturation point is reached and we realize that no new themes are emerging.

##### Qualitative analysis

A thematic content analysis method will be used to analyze the transcribed interviews following a systematic, iterative process. Codes will be applied to the transcripts, and converted into categories to represent the main themes arising from the data [37]. A small number of interviews will be analyzed independently by two other members of the research team. Themes emerging from the analyses of interviews by independent researchers will be compared and contrasted with others constantly. Triangulation of themes and concepts will be used to further compare and contrast the data from the different participating groups. This will enhance the reliability and validity of the analysis.

##### Quantitative Analysis

An intention to treat analysis will be carried out. Both parametric and non-parametric tests will be used for data analysis. Mean and standard deviation scores for all continuous measures shall be presented, and normality will be assessed using Kolmogrov-smirnov test for normality. Spearman's correlation coefficient shall be used to measure associations among different measures. Baseline differences will be measured using a t test for normative data and Chi square test for categorical data. This will enable us to take into account any baseline differences in our final analyses. Differences between the treatment and the control group will be measured using linear regression, while controlling for baseline differences.

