## Methods

We will conduct a pilot randomized controlled trial of culturally adapted manual assisted Problem Solving Therapy (C- MAPS) in British South Asian females who self harm. Ethical approval was obtained from Tameside &Glossop Local Research Ethics Committee for the study (REC Reference number: 08/H1013/6). The intervention will be assessed using a prospective rater blind randomized controlled design, with an experimental and a control treatment as usual (TAU) group. Face to face baseline interviews followed by 3 months outcome assessments will be carried out. Further six months follow up assessments will be through post or telephone. A sub group of participants will be invited for in depth qualitative interviews exploring about barriers accessing mental healthcare and family dynamics.

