### Recruitment plan

The study will be conducted at the emergency departments of Royal Blackburn, North Manchester General and Manchester Royal Infirmary hospitals and GP practices that cover areas with large South Asian population. We will be using culturally appropriate strategies to promote the trial. Liaison with the community has already been initiated through awareness talks in partnership with the voluntary sector organizations. These voluntary organizations were also invited to comment on the design of the trial and content of the intervention. Information about the study in the form of posters and information sheets in the four study languages (Urdu, Hindi, Punjabi and English) will be made available. The therapists in the team are also proficient in these south Asian languages. The research team will also conduct regular liaison meeting with the emergency department, crisis team staff and GP practices to promote the study within the departments.

Consecutive patients meeting inclusion criteria will be informed about the study by the clinician who will take verbal or written consent for the research team to make the contact.

The study will be explained to each participant in detail by a researcher and written consent will be obtained. Family participation will be encouraged but only with participants' permission. For randomization the researcher will refer to an allocation sequence that will be provided by the offsite trial statistician and based on a computer generated list of random numbers. Even if there is more than fifty percent refusal we expect sufficient number of patients each assigned to C- MAPS or the treatment as usual group.

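### Covariate adjustment appears to hinge on baseline significance tests between small randomised arms; fixing the baseline score as a covariate would protect precision at almost no cost

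*Protocol article*

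**What the plan says.** All of the relevant text is in the Quantitative Analysis section of the protocol article, in three consecutive sentences.

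- The comparison at baseline: "Baseline differences will be measured using a t test for normative data and Chi square test for categorical data".
- The purpose given for it: "This will enable us to take into account any baseline differences in our final analyses".
- The treatment comparison: "Differences between the treatment and the control group will be measured using linear regression, while controlling for baseline differences".

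No significance level is attached to the baseline tests. On size, the Sample Size section says "A total of thirty participants will be recruited to the pilot" and expects that, after losses, "we will have at least 10 subjects per group for analysis". Under Recruitment plan, allocation follows a sequence "based on a computer generated list of random numbers". The primary outcome is the Beck scale for suicidal ideation, described as "A 21-item self-report questionnaire used to detect and measure severity of suicide ideation". The Methods section provides for a baseline visit: "Face to face baseline interviews followed by 3 months outcome assessments will be carried out".

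**The concern.** The middle sentence gives the baseline tests a task: they are what allows imbalance to be handled in the final model. A statistician following this text would test each baseline variable and adjust for those that differ.

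There are two problems with that. First, if allocation is properly random, any baseline difference arose by chance, so a test of whether it arose by chance answers nothing. Second, a covariate earns its place by predicting the outcome, not by differing between arms. A prognostic score that happens to be fairly balanced still removes outcome variance when it is in the model, and a test-driven rule discards that gain.

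What is at stake is the precision of the treatment estimate. The Aims and objectives section wants an effect size to plan the definitive trial and a preliminary look at whether there is a treatment effect. With this few women, avoidable noise in that estimate passes directly into the next trial's planning.

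**Working it through.** **Inputs from the protocol article.** 30 recruited and at least 10 per group analysed (Sample Size); two randomised groups (Sample Size, Recruitment plan); t test for baseline scores and linear regression for outcome (Quantitative Analysis).

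**Assumptions, none of them stated in the document.** Two-sided 0.05 as the cut-off for a baseline difference; 1:1 allocation, so that 30 recruited means 15 per arm before losses; normally distributed scores; baseline-outcome correlation ρ of 0, 0.3, 0.5 or 0.7.

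**The plan's own figure.** 20 analysed women grow to 20/(1 − 1/3) = 30 if one third are lost. The stated total is therefore consistent with a loss of up to one third. No loss rate is given, so this is a consistency check, not a reproduction. I use 10 and 15 per arm as the two ends.

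**Step 1: imbalance needed for a significant baseline test.** Smallest significant difference in SD units = t(0.975, 2n − 2) × √(2/n).
- n = 10: 2.101 × 0.447 = 0.94 SD
- n = 15: 2.048 × 0.365 = 0.75 SD

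**Step 2: how often a given score would be adjusted for.** Under randomisation the test is significant in 5% of trials, so the score stays out of the model in about 95%.

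**Step 3: how often a sizeable imbalance would be passed over.** P(|difference| ≥ 0.5 SD) = 2 × [1 − Φ(0.5/√(2/n))].
- n = 10: 0.5/0.447 = 1.118, giving 26%
- n = 15: 0.5/0.365 = 1.369, giving 17%

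In simulation, the imbalance is that large but not significant in about 21% (n = 10) and 12% (n = 15) of all trials.

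**Step 4: cost in precision.** 100,000 simulated trials per setting compare adjusting only when baseline p<0.05 (the rule) with always adjusting. SDs of the treatment estimate are in outcome SD units.

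| n per arm | ρ | SD, rule | SD, always adjust | Ratio | Type I error, rule |
|---|---|---|---|---|---|
| 10 | 0 | 0.452 | 0.461 | 0.98 | 5.0% |
| 10 | 0.3 | 0.446 | 0.439 | 1.02 | 4.8% |
| 10 | 0.5 | 0.437 | 0.400 | 1.09 | 4.4% |
| 10 | 0.7 | 0.420 | 0.329 | 1.28 | 3.7% |
| 15 | 0 | 0.367 | 0.372 | 0.99 | 5.1% |
| 15 | 0.3 | 0.363 | 0.355 | 1.02 | 4.8% |
| 15 | 0.5 | 0.353 | 0.322 | 1.10 | 4.3% |
| 15 | 0.7 | 0.342 | 0.266 | 1.29 | 3.6% |

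Always adjusting gives a type I error of 4.9-5.0% throughout.

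**Check on the always-adjust column.** SD = √[(2/n)(1 − ρ²)(1 + 1/(2n − 4))]. For n = 15, ρ = 0.5: √(0.1333 × 0.75 × 1.0385) = 0.322. For n = 10, ρ = 0: √(0.2 × 1.0625) = 0.461. Both agree with the simulation.

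**The case against.** The best defence is that the simulated rule is not written in the plan. There is no cut-off; the text speaks of any differences, not significant ones; and the final sentence is unconditional. It can fairly be read as ordinary baseline-adjusted regression, with the tests serving only the baseline table. This stands in part: the 95% figure and the precision losses describe one reading under an assumed 0.05 level. It does not remove the point, because the preceding sentence makes the tests the route to adjustment. If routine adjustment is meant, the text should say so.

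A second objection is that covariate lists are commonly left to an analysis plan, which is not shown here. I agree, and the absence of a list is not the complaint. The complaint is the selection rule that the article does state, which an analysis plan faithful to it would inherit.

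Third, the simulation has a single covariate, whereas the trial measures several scales. With 5 to 10 independent variables, the chance that at least one is flagged is 1 − 0.95⁵ = 23% to 1 − 0.95¹⁰ = 40%. If a flagged variable is prognostic, some precision returns. That is true, but which variable enters is then a matter of chance.

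Three stronger readings are tempting, and the documents support none of them.

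- A reader might infer that the error rate is compromised. The departure is downwards, to 3.6-4.4% at correlations of 0.5-0.7, so false positives are not inflated. Nothing here shows bias across randomisations.
- A reader might infer that the baseline suicidal ideation score will be left out in 95% of trials as a settled fact of this plan. That needs both the conditional reading and the 0.05 cut-off.
- A reader might infer a large loss of power. That needs a target effect, and the document states neither an effect nor a power. This is a 30-woman pilot with preliminary aims, and no confirmatory claim rests on the regression.

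**Conclusion.** The concern holds in moderate form. The text ties adjustment to observed baseline differences, or can be read to do so. That criterion is wrong under randomisation, and at 10 to 15 women per arm only very large imbalances would trigger it.

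The size depends mainly on a correlation that the document does not give. The loss of precision is negligible at 0.3 (about 2%), noticeable at 0.5 (9-10%) and considerable at 0.7 (28-29%). At zero the comparison reverses by 1-2%. These figures also rest on the assumed 0.05 cut-off, 1:1 allocation and normal scores.

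The harm is a noisier effect size and a model that depends on the data, not false positives. This is a cheap improvement that should be made; it is not a defect that invalidates the pilot.

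**What to change.** Drop the baseline significance tests and report baseline characteristics descriptively by arm. Replace the last sentence of the Quantitative Analysis section with wording such as: *Each continuous outcome will be compared by linear regression of the follow-up score on randomised arm and the baseline value of the same score, whatever the observed baseline difference.* This settles the matter under either reading of the present text.

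The cost is one sentence and one degree of freedom per model, and a 1-2% loss of precision if the baseline score turns out not to predict the outcome. The baseline interview is already planned, so no extra visit is needed.
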